### Statistical analysis

All statistical analyses will be performed using SPSS v27.0 (IBM Corp., USA) and R v4.3.0 or later. Baseline characteristics will be summarized using descriptive statistics: continuous variables as mean ± SD or median (IQR) depending on normality, and categorical variables as frequencies and percentages. Group comparisons (ctDNA-positive vs ctDNA-negative) will use Student’s t-test or Mann-Whitney U test for continuous variables, and χ² or Fisher’s exact test for categorical variables.

Longitudinal ctDNA changes will be analyzed using generalized estimating equations (GEE) or linear mixed-effects models to account for repeated measures, adjusted for baseline covariates such as FIGO stage, tumor size, and nodal status. PFS and OS will be estimated by Kaplan-Meier method and compared with log-rank tests; hazard ratios (HRs) with 95% CIs will be obtained from univariate and multivariate Cox proportional hazards models. Covariates in multivariate models will be checked for collinearity (VIF >5) and proportional hazards assumption (Schoenfeld residuals).

Predictive performance of ctDNA for recurrence will be evaluated using ROC curves (AUC, sensitivity, specificity, PPV, NPV); optimal cut-offs for continuous ctDNA will be determined via Youden’s index. Concordance between ctDNA and imaging will be assessed with Cohen’s kappa. Missing data<20% will be handled by multiple imputation (MICE), with sensitivity analyses including complete-case analyses. Patients lost to follow-up will be censored at the last known date. Two-sided p-values<0.05 indicate statistical significance, with multiple testing correction applied for secondary endpoints. Exploratory subgroup analyses may be conducted by FIGO stage, histology, or baseline HPV type. These subgroup analyses will be exploratory and hypothesis-generating and will not be used for confirmatory subgroup inference.

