#### Withdrawal criteria

Participants may be withdrawn from the study under the following circumstances:

voluntary withdrawal of informed consent for any reason at any time without prejudice to future medical care;inability to complete the planned treatment regimen due to unacceptable toxicity or deteriorating performance status;inability to comply with the follow-up schedule or protocol requirements as judged by the investigator;occurrence of severe adverse events (SAEs) requiring permanent discontinuation of CCRT, such as grade 4 hematologic toxicity, grade 3–4 non-hematologic toxicity not manageable with supportive care, or life-threatening complications;major protocol violations that compromise data integrity or patient safety, such as failure to obtain required blood samples at critical time points or deviation from prescribed treatment regimens;development of disease progression requiring change in treatment approach during the planned CCRT course;investigator’s judgment that continued participation is not in the patient’s best interest based on medical, safety, or ethical considerations.

Data collected from withdrawn participants up to the point of withdrawal will be included in the analysis according to the intention-to-treat principle unless consent for data use is specifically withdrawn.

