### Outcome measures

The primary outcome of this study is progression-free survival (PFS), defined as the time from the date of initiation of CCRT to the date of first documented disease progression (according to RECIST 1.1 criteria on imaging studies or histopathologic confirmation), disease recurrence (appearance of new lesions after achieving CR), or death from any cause, whichever occurs first. Patients who are alive and progression-free at the time of analysis will be censored at the date of their last adequate tumor assessment.

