Secondary outcome include: (1) Overall survival (OS), defined as the time from the initiation of CCRT to death from any cause, with patients who are alive at the time of analysis censored at the date they were last known to be alive; (2) Objective response rate (ORR), defined as the proportion of patients achieving CR or PR at the first imaging assessment (3 months post-CCRT) according to RECIST version 1.1 criteria; (3) Dynamic changes in plasma HPV ctDNA levels expressed as continuous variables (copies per mL) and categorical variables (detectable versus undetectable) at predefined time points (T0, T1, T2, T3, and follow-up time points) during and after CCRT, including assessment of ctDNA clearance kinetics (time to first undetectable ctDNA), nadir ctDNA levels, and patterns of ctDNA dynamics (rapid clearance, slow clearance, persistent detection, or reappearance after initial clearance); (4) Predictive performance of HPV ctDNA for disease recurrence, including calculation of sensitivity (proportion of patients with recurrence who have detectable ctDNA), specificity (proportion of patients without recurrence who have undetectable ctDNA), positive predictive value (PPV; probability of recurrence given detectable ctDNA), negative predictive value (NPV; probability of no recurrence given undetectable ctDNA), and area under the receiver operating characteristic curve (AUC-ROC) for ctDNA as a predictive biomarker, with 95% confidence intervals (CIs); and (5) Concordance between HPV ctDNA status and imaging-based assessment (MRI and/or PET-CT) in detecting residual disease at 3 months post-CCRT and early relapse during follow-up, assessed using Cohen’s kappa statistic and contingency table analysis. Additionally, we will explore the lead time advantage of ctDNA detection, defined as the time interval between ctDNA-detected recurrence and imaging-detected recurrence in patients who experience disease progression (20). The detailed schedule of assessments follows the SPIRIT framework and is presented in **Table 1**, which outlines all study procedures, evaluations, and time points from screening through close-out.

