### Sample size calculation

The sample size was calculated based on the primary endpoint of 2-year progression-free survival (PFS), comparing patients with detectable versus undetectable plasma HPV ctDNA at 3 months after completion of CCRT (T3). Institutional historical data indicate a 2-year PFS of approximately 75% in the ctDNA-negative group, while published studies suggest a rate of approximately 50% in the ctDNA-positive group (21). Based on prior studies of HPV-associated malignancies, we conservatively estimated that 30% of patients would be ctDNA-positive at the T3 assessment. Sample size was estimated using the log-rank test for comparing survival curves between two groups: 
$\text{n}={\left({\text{Z}}_{1}-\alpha {/}_{2}+{\text{Z}}_{1}-\beta \right)}^{2}/\left[{\left(\ln\text{HR}\right)}^{2}\times \text{p}\left(1-\text{P}\right)\right]$.

where 
$Z_{1-\alpha /2}=1.96$ for a two-sided α = 0.05, 
$Z_{1-\beta }=0.842$ for 80% power, and *p* = 0.30 represents the proportion of patients expected to be ctDNA-positive. The hazard ratio (HR) was derived from the assumed survival probabilities (
$S_{\text{ctDNA}+}=0.50$, 
$S_{\text{ctDNA}-}=0.75$), yielding an estimated HR of 2.41. Using these assumptions, a minimum of 48 evaluable patients is required to achieve 80% power to detect a difference in 2-year PFS at a two-sided significance level of 0.05. Allowing for an anticipated 15% attrition rate, the total target enrollment is 57 patients. This sample size is considered feasible for recruitment at a single high-volume tertiary cancer center over the planned 2-year enrollment period and is supported by effect sizes reported in prior studies of ctDNA as a prognostic biomarker in HPV-associated cancers (21, 22).

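### The unscoped MICE rule, as written, reaches T3 ctDNA status and 3-month response even for patients who died or progressed before T3

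*Protocol article*

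**What the plan says.** All places are in the protocol article.

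- **Statistical analysis:** "Missing data<20% will be handled by multiple imputation (MICE), with sensitivity analyses including complete-case analyses". The imputed analysis is thus the main one and complete case the check. No variable, patient group or reason for missingness is named. The same section censors patients lost to follow-up, so PFS and OS times are not themselves imputed.
- **Sample size calculation:** the primary comparison is of PFS, "comparing patients with detectable versus undetectable plasma HPV ctDNA at 3 months after completion of CCRT (T3". The section plans 48 evaluable patients, 15% attrition and 57 enrolled.
- **Outcome measures:** PFS is "defined as the time from the date of initiation of CCRT to the date of first documented disease progression", or recurrence or death, so an event can precede T3. No landmark or at-risk-at-T3 rule is given. ORR is "the proportion of patients achieving CR or PR at the first imaging assessment (3 months post-CCRT" visit, with no rule for patients who lack that assessment.
- **Withdrawal criteria:** the listed reasons include "development of disease progression requiring change in treatment approach during the planned CCRT course" and "failure to obtain required blood samples at critical time points". Unless consent for data use is withdrawn, "Data collected from withdrawn participants up to the point of withdrawal will be included in the analysis according to the intention-to-treat principle".

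**The concern.** Each statement is ordinary alone. Together they put patients without a T3 measurement into an analysis whose groups are defined at T3, and the only stated way of handling the gap is imputation.

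Two quantities are exposed. The first is the grouping variable of the primary comparison. A patient who died during or soon after CCRT never had a T3 ctDNA status, so a filled-in value estimates nothing. The second is 3-month response. A patient who failed before the scan has no RECIST reading at that visit, yet her result is known in substance. Treating it as unknown and borrowing from patients who were scanned, or dropping her as the complete-case analysis does, raises ORR.

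The rule is likely to act mainly on values measured after baseline, because stage, histology and HPV16/18 status are eligibility requirements and should be nearly complete.

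**Working it through.** **1. The plan's own figures.** HR = ln(0.50)/ln(0.75) = 2.41. With p = 0.30, (1.96 + 0.842)² / [(ln 2.41)² × 0.30 × 0.70] = 48.3, given as 48. Then 48/0.85 = 56.5, rounded up to 57. The arithmetic reproduces. (Whether 48 should be read as patients or as events is a separate matter and is not used here.)

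**2. Does the 20% rule apply at the planned attrition?** 57 − 48 = 9, and 9/57 = 15.8%, so yes. The rule still applies at 11/57 = 19.3% and stops at 12/57 = 21.1%. The protocol does not say how much of the attrition falls before T3.

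**3. Primary HR (illustration).** From the plan: 30% positive and 2-year PFS of 50% and 75%. Assumed: exponential hazards −ln(0.50)/24 and −ln(0.75)/24 per month from month 4.5 to month 24, and a further 5%, 10% or 15% of all patients with an event between months 1 and 4.5, whose T3 status is then imputed. Simulated n = 20,000.

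| Share with pre-T3 event | HR, outcome not in imputation model | HR, outcome in imputation model | Early events as share of all events |
|---|---|---|---|
| 5% | 2.22 | 2.57 | 16% |
| 10% | 1.91 | 2.38 | 29% |
| 15% | 1.75 | 2.51 | 39% |

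The last column can be checked by hand. Over 19.5 months the event probabilities are 1 − 0.50^(19.5/24) = 0.431 and 1 − 0.75^(19.5/24) = 0.208, so the mix is 0.3 × 0.431 + 0.7 × 0.208 = 0.275. At 5%, 0.05/(0.05 + 0.95 × 0.275) = 16%.

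A repeat without the outcome gave about 2.1, 1.9 and 1.8, against about 2.3–2.4 in patients at risk at T3. A further run at the trial's size (n = 57, with 3, 6 or 9 early events and about 100 runs per setting, so noisy) agrees in direction:

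- Outcome omitted: median HR 2.02, 1.93 and 1.86, against 2.28, 2.38 and 2.51 in patients at risk at T3. About 31% of the imputed patients were labelled positive.
- Outcome included: 2.53, 2.19 and 2.46, against 2.54, 2.34 and 2.56. About 52% were labelled positive. The HR roughly survives because the early event itself pushes the patient into the positive group.

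**4. ORR (illustration).** Assume 90% response among assessed patients and k patients who failed before the scan. Imputing from assessed patients alone, or dropping the k, gives about 90%. Counting them as non-response gives 0.90 × (57 − k)/57:

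- k = 3: 48.6/57 = 85.3%
- k = 6: 45.9/57 = 80.5%
- k = 9: 43.2/57 = 75.8%

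At an assumed 80% among assessed patients, the same counts give 75.8%, 71.6% and 67.4%. The gap is about 4 to 14 points across the two assumptions. The protocol gives neither an expected ORR nor a count of pre-T3 failures.

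**The case against.** The strongest reply is that the protocol nowhere says T3 status or response will be imputed. The list of variables and the imputation model are normally left to a statistical analysis plan, which is not shown. The word *evaluable* in the sample size section suggests that patients without T3 status may simply be left out. Retaining data up to withdrawal means retaining what was observed. A patient who progressed during CCRT has a recorded progression, and on an ordinary reading of the ORR definition she did not achieve CR or PR. The complete-case analysis already drops patients without T3 status from the primary comparison.

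Much of this stands, and it limits the point in three ways:

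- A reader might infer that the trial *will* impute T3 status. The text covers that case but does not state it.
- A reader might infer that the imputed values would be favourable. That is not a property of MICE. It depends on whether the outcome and earlier ctDNA enter the model, and with the outcome included the HR is roughly kept.
- A reader might infer that nobody who left before T3 should be imputed. That is too broad. A patient alive and progression-free with a missed or failed sample has a real but unobserved value, and imputing it can be legitimate. A patient who progressed might even still be sampled, since the stop at progression is written for the later follow-up samples.

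The reply does not remove the rest. The sentence is an active rule with no exemption, and complete case is only its sensitivity analysis. *Evaluable* points to exclusion, the withdrawal text to retention and the missing-data sentence to imputation, so the primary analysis set is unsettled. For ORR, the complete-case analysis drops the same failures.

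**Conclusion.** The point holds as a defect in a stated rule. Followed literally, the rule assigns a T3 ctDNA status to patients who died or progressed before T3, and it allows 3-month response to be imputed for early failures. Neither form of imputation supports a prognostic claim for a marker measured at T3. Without the outcome, the HR falls from about 2.4 to about 1.8–2.2 when 5–15% of patients have earlier events. With the outcome, the HR is about kept, but the exposure is partly inferred from the event it is meant to predict. ORR could be overstated by about 5, 10 or 14 points with 3, 6 or 9 unscanned early failures.

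These sizes are illustrations. The 90% response rate, the failure counts and the share of pre-T3 events are assumptions, and the 15% attrition may include patients lost after T3 or for reasons unrelated to the disease. The need to settle the rule does not depend on them.

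**What to change.** Change the wording as follows:

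- Define the primary T3 analysis set as patients alive and progression-free at T3. State how T3 is dated, because the T3 sample and the first scan share a ±2-week window.
- Do not impute T3 ctDNA status for patients with a PFS event before T3. Report them separately, with reasons and outcomes.
- For ORR, count death or documented progression before the first assessment as non-response, with all patients who started CCRT as the denominator.
- Limit MICE to covariates and to values that exist but were not observed, such as a missed or QC-failed T3 sample in a patient alive and progression-free.
- Replace the reference to intention-to-treat with a statement that all patients who started CCRT are accounted for.

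The cost is protocol and analysis-plan text only, and recruitment is not planned to begin until January 2027. The number in the primary comparison and the ORR may become slightly less favourable.

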### Data management and quality control

All study data will be recorded electronically using a secure, validated EDC system (REDCap, Tianjin Medical University) with password-protected, role-based access and comprehensive audit trails. Source documents (CRFs, lab and imaging reports, medical records) will be retained on-site in accordance with GCP and institutional policies. Study personnel will undergo standardized training on eligibility assessment, study procedures, sample handling, CRF completion, and blinding, with documentation of competency. Centralized data monitoring will occur quarterly by an independent CRA, and on-site source data verification will be conducted at least twice per year. Data queries will be resolved promptly through the EDC system, with all corrections documented. An independent Data Safety Monitoring Committee (DSMC), comprising at least three experts in gynecologic oncology, radiation oncology, and biostatistics, will review safety data every 6 months or after enrollment of every 20 patients, and provide recommendations on study continuation, modification, or termination.

## Discussion

This prospective cohort study protocol establishes a systematic framework for evaluating HPV ctDNA as a dynamic biomarker in LACC patients receiving CCRT. The integration of serial ctDNA monitoring throughout the treatment continuum—from baseline through post-treatment follow-up—enables comprehensive assessment of tumor burden dynamics and early identification of molecular residual disease before clinical or radiographic manifestations become apparent. This approach addresses a critical unmet need in cervical cancer management, as conventional imaging modalities often demonstrate delayed sensitivity for residual microscopic disease and limited ability to distinguish post-treatment inflammatory changes from viable tumor tissue.

The translational implications of HPV ctDNA monitoring are substantial. First, the tumor-specific nature of HPV DNA sequences integrated into cancer cell genomes provides exceptional analytical specificity, as these viral sequences are absent from normal human cells and high-grade intraepithelial lesions (7). Second, the ability to detect molecular residual disease before radiographic progression enables potential treatment intensification or salvage therapy during the window of minimal tumor burden, when therapeutic interventions may be most effective. Recent data demonstrate detection rates of 69% at baseline in LACC patients, with strong correlation between plasma HPV ctDNA levels and tumor burden (7), suggesting that quantitative ctDNA measurements may serve as surrogate markers for tumor volume dynamics throughout treatment.

### Strengths of the study

This protocol incorporates several methodological strengths that enhance its scientific rigor and potential clinical impact. The prospective design with standardized treatment protocols and predefined blood sampling time points ensures internal consistency and minimizes ascertainment bias inherent in retrospective analyses. Serial quantitative monitoring using ddPCR technology provides high analytical sensitivity (lower limit of detection<10 copies per reaction) and precision for low-abundance targets without requiring standard curves (8). The integration of ctDNA data with comprehensive clinical, imaging, and pathological assessments enables robust multivariable analyses to determine independent prognostic value while controlling for established risk factors. Furthermore, the exploratory NGS analysis in a subset of patients facilitates validation of ddPCR findings and assessment of tumor-specific somatic mutations that may associate with treatment resistance, generating hypothesis-generating data for future mechanistic investigations.

The anticipated findings from this study may inform risk-adapted surveillance paradigms and future therapeutic strategies. Patients with rapidly cleared HPV ctDNA and sustained undetectable status may potentially undergo de-escalated follow-up with reduced imaging frequency, improving quality of life while maintaining surveillance efficacy. Conversely, those with persistent or reappearing ctDNA warrant intensified monitoring and consideration for clinical trials evaluating consolidation therapies such as immune checkpoint inhibitors, which have demonstrated efficacy in recurrent/metastatic settings (23). The recent integration of ctDNA monitoring into large randomized trials, including biomarker substudies within CALLA (durvalumab) and KEYNOTE-A18 (pembrolizumab), exemplifies the growing recognition of molecular assessment in clinical decision-making (24, 25).

### Feasibility and limitation

As a single-center study, external generalizability may be constrained by institutional practice patterns, patient demographics, and technical expertise in ctDNA analysis. Future multicenter studies across different regions, laboratories, and detection platforms will be required to externally validate the ddPCR thresholds, ctDNA clearance patterns, and predictive performance observed in this study. While the calculated sample size of 57 patients provides 80% power for the primary endpoint, subgroup analyses stratified by FIGO stage, histologic subtype, or baseline HPV type will have limited statistical power. Therefore, these analyses will be considered exploratory and hypothesis-generating, rather than confirmatory, and will mainly inform the design of future larger studies. The 24-month follow-up duration, while sufficient to capture most early recurrences, may inadequately characterize late relapses occurring beyond 2 years, particularly in patients achieving complete response. Long-term clinical follow-up will continue after completion of the planned 24-month study period, and updated analyses of long-term PFS, OS, and late recurrence patterns will be conducted in future reports. Pre-analytical variability represents another potential limitation; despite standardized protocols for blood collection, processing, and storage, factors such as hemolysis, delayed processing beyond 2 hours, or degradation during freeze-thaw cycles could influence ctDNA recovery and quantification (26). The absence of randomization precludes causal inference regarding ctDNA-guided therapeutic interventions, limiting the ability to demonstrate whether acting on ctDNA results improves outcomes compared to standard surveillance alone.

Technical challenges in liquid biopsy implementation also warrant acknowledgment. Although ddPCR offers superior sensitivity compared to traditional methods, detection rates remain imperfect, with approximately 30-40% of LACC patients testing negative at baseline despite confirmed HPV-positive tumors (27). This heterogeneity may reflect biological factors (tumor shedding kinetics, vascular invasion patterns), technical variables (HPV genotype distribution, assay design limitations), or disease characteristics (tumor size, stage). Furthermore, standardization across different platforms and laboratories remains challenging, as demonstrated by variability in detection thresholds, quality control metrics, and quantification algorithms reported across studies (28). The field requires consensus on analytical validation criteria, reporting standards, and clinical decision thresholds before widespread implementation can be achieved.

This prospective cohort study will evaluate the clinical utility of HPV ctDNA as a dynamic biomarker for treatment response and prognosis in LACC. By using standardized protocols and comprehensive outcome assessments, it aims to address key knowledge gaps, support personalized post-CCRT surveillance, identify patients at high risk of recurrence, and inform future ctDNA-guided interventional trials, advancing precision oncology in cervical cancer.

